# A novel mindful-compassion art therapy (MCAT) for reducing burnout and promoting resilience for end-of-life care professionals: a waitlist RCT protocol

**DOI:** 10.1186/s13063-019-3533-y

**Published:** 2019-07-08

**Keywords:** Burnout, Resilience, Mindful compassion, Art therapy, Multimodal intervention, End-of-life care, Palliative care, Randomized control trial

## Abstract

**Introduction:**

End-of-life (EoL) care professionals are prone to burnout given the intense emotional nature of their work. Previous research supports the efficacy of art therapy in reducing work-related stress and enhancing emotional health among professional EoL caregivers. Integrating mindfulness meditation with art therapy and reflective awareness complementing emotional expression has immense potential for self-care and collegial support. Mindful-compassion art therapy (MCAT) is a novel, empirically informed, and highly structured intervention that aims to reduce work-related stress, cultivate resilience, and promote wellness. This study aims to assess the potential effectiveness of MCAT for supporting EoL care professionals in Singapore.

**Methods:**

This is an open-label waitlist randomized controlled trial. Sixty EoL care professionals, including doctors, nurses, social workers, and personal care workers, are randomly allocated to one of two groups: (i) an intervention group that receives MCAT immediately and (ii) a waitlist-control group that receives MCAT after the intervention group completes treatment. Face-to-face self-administered outcome assessments are collected at three different time points—baseline (T1) for both groups, post-intervention (T2), and 6-week follow-up (T3) for intervention group—as well as pre-intervention (T2) and post-intervention (T3) for the waitlist-control group. The primary outcome measure is burnout, and secondary measures include emotional regulation, resilience, compassion, quality of life, and death attitudes. Between- and within-participant comparisons of outcomes are conducted, and the appropriate effect size estimates are reported. An acceptability and feasibility study is to be conducted by using a triangulation of qualitative data with framework analysis.

**Discussion:**

The outcomes of this study will contribute to advancements in both theories and practices for supporting professional EoL caregivers around the world. It will also inform policy makers about the feasibility, acceptability, and effectiveness of delivering a multimodal psycho-socio-spiritual intervention within a community institutional setting. The study has received ethical approval from the institutional review board of Nanyang Technological University.

**Trial registration:**

ClinicalTrials.gov Identifier: NCT03440606. Retrospectively registered February 21, 2018.

**Electronic supplementary material:**

The online version of this article (10.1186/s13063-019-3533-y) contains supplementary material, which is available to authorized users.

## Background

Professional caregivers working in the fields of end-of-life (EoL), palliative, and bereavement care are regularly exposed to immense stress from intense emotional engagements with dying patients and bereaved families [1]. The constant exposure to death, grief, and loss can result in burnout [2, 3], “a state of exhaustion in which one is cynical about the value of one’s occupation and doubtful of one’s capacity to perform” [4]. Burnout combined with the vicarious trauma experienced by professional EoL caregivers through the deaths of their patients can further result in compassion fatigue, “an extreme state of tension and preoccupation with the suffering of those being helped to the degree that it can create a secondary traumatic stress for the helper” [5]. If not properly managed, burnout and compassion fatigue can be detrimental to the physical and mental health of professional EoL caregivers, and effects can trickle down to patients, colleagues, family, and friends and pose threats to quality of patient care and quality of personal life.

A recent study found that about 9% of the 7905 surgeons surveyed in the US reported having made a major medical error in the previous 3 months [6] and that stress and burnout were the principal culprits of safety-related quality-of-care concerns [7]. Another study reported that, owing to stress and burnout, the turnover rate of in-patient hospice workers stands at an alarming 30% and reaches as high as 60% for homecare workers [8]. Professional EoL caregiving, by its very nature, necessitates high levels of psycho-socio-emotional competence and therefore adequate support to professional EoL caregivers would entail clinical supervisions or interventions that aim to enhance their sense of autonomy and empathic capacity while providing avenues to cultivate resilience, foster coherence, and achieve meaning-making [9]. Of particular importance is establishing a communal platform for EoL care professionals to periodically reflect on their own attitudes, feelings, and anxieties related to death and loss [10] while being able to express their thoughts to team members for building mutual respect, understanding, and communal support [11].

### Clinical supervision and art therapy

Although supervision has been shown to be effective in reducing fatigue among hospice workers [12], specific attention to emotion-focused coping skills has proven more effective than problem-focused strategy skills in reducing burnout [13]. Emotion-focused supervision requires professionals to consider and communicate feelings and experiences that may be difficult to verbalize. As art provides the means to express oneself through images and metaphors that transcend the barriers of language [14], emotion-focused supervision that incorporates expressive art techniques for self-reflection and self-expression can promote and enhance the understanding of one’s emotions and stress [15]. In other words, supervised art therapy allows art-making and creativity to take central roles in professional self-understanding [16]. Several art therapists have documented how their work with EoL care professionals prevented and reduced burnout by managing stress, fostering collegial connections, emphasizing self-care, and enabling the expression of grief [17, 18].

To better support professional EoL caregivers with work-related stress in Asia, our research team had previously designed a novel art therapy–based supervision model that aimed at alleviating burnout, nurturing emotional awareness, increasing collegial connections, and allowing a safe space to reflect on death and loss [19]. The efficacy of this model was tested through a quasi-experimental design (*n* = 132); 69 participants were enrolled in an 18-h art therapy–based supervision group (run in 6 consecutive weekly sessions lasting 3-h each) and 63 participants were enrolled in an 18-h standard skills–based supervision group (run in 3 consecuitve daily sessions lasting 6-h each). Pre- and post-intervention assessments of participants’ levels of burnout, emotional regulation, and death attitudes revealed significant reductions in exhaustion and death anxiety as well as significant increases in emotional awareness for those enrolled in the art therapy supervision group [20]. This study provided strong evidence that art therapy–based supervision is effective in enhancing emotional regulation, fostering meaning-making, and promoting self-reflection [21].

### Mindfulness practice and art therapy–based supervision

In the past decade, both researchers and clinicians have become increasingly interested in mindfulness practice as studies continue to reveal its beneficial effects [22]. Jon Kabat-Zinn, the foremost pioneer in the therapeutic application of mindfulness, defines it as “the awareness that emerges through paying attention on purpose, in the present moment, and nonjudgmentally to the unfolding of experience moment to moment” [23]. Bishop et al. elaborated that mindfulness is “characterized by curiosity, openness, and acceptance” [24]. Essentially, mindfulness requires individuals to practice a concentrated focus on the present moment, to immerse oneself in his or her immediate experience, and to be freed of the destructive thoughts of future worries and past regrets, so as to attain greater clarity, self-acceptance, and ultimately an enhanced compassion for self and others. As such, the practice of mindfulness can attune seamlessly with the emotional and spiritual needs of those who work with death and loss on a consistent basis.

The literature has provided a robust pool of evidence supporting the efficacy of mindfulness practice and self-compassion in promoting psychological well-being [25], reducing depression and anxiety [26], and enhancing health and overall physical functioning [27]. Despite these positive findings, relatively little research has attempted to integrate mindfulness practice with art therapy to investigate their combined effects for health elevation and stress reduction, an endeavor that warrants much greater attention [28]. The introspective and intuitive foundation of mindfulness practice can complement and facilitate the expressive and creative foundation of art therapy, and vice versa. A unique amalgamation of these two modalities in the context of supportive intervention for EoL care professionals has immense potential to aid them in coping with and rising above the trauma of loss and grief that they face on a daily basis.

In essence, the integration of art therapy and mindfulness practice for addressing the self-care needs of professional EoL caregivers is a scarcely explored area in the field of palliative, hospice, and bereavement care. Building on the clinical foundation of art therapy–based supervision [19–21], a novel mindful-compassion art therapy (MCAT) for clinical supervision was developed. MCAT is a highly structured, multimodal, group-based intervention that aims at creating a supportive platform for EoL care professionals to deeply reflect on and creatively express their experiences of stress and self-care, competence and challenges of caregiving, and the emotionality of loss and grief. It is hypothesized that these interactive processes will serve to foster self-understanding, connectedness, internal strength, and compassion among participants in MCAT, so as to derive a renewed appreciation of the meaning of work as well as enhanced quality of life. The ultimate goal of MCAT is to offer a viable supported self-care intervention to alleviate burnout and cultivate sustained resilience for EoL care professionals in the global context.

## Aim and objectives

Based on the Medical Research Council guidance for developing and evaluating complex intervention [29], the aims of the present study are to assess the feasibility, acceptability, and potential effectiveness of MCAT in reducing burnout and promoting resilience and holistic wellness among a purposive sample of EoL care professionals in Singapore. The specific objectives are the following:to assess the effectiveness of MCAT for reducing burnout and negative death attitudes among EoL care professionals, including hospice and palliative care physicians, nurses, social workers, and allied health workers;to assess the effectiveness of MCAT for increasing EoL care professionals’ self-perceived levels of emotional regulation, resilience, compassion, and quality of life;to assess the feasibility and acceptability of MCAT as a supportive self-care program for EoL care professionals in the context of Singapore; andto develop a standardized protocol for further empirical research that tests intervention effectiveness, feasibility, and acceptability of MCAT in other international contexts.

## Methods

### Study design

This study will adopt an open-label waitlist randomized control trial (RCT) design comprising two groups: (i) an intervention group (which receives MCAT immediately after baseline assessment) and (ii) a waitlist-control group (which receives MCAT immediately after the intervention group completes treatment). A waitlist RCT is chosen on the basis of the ethical principle of justice as the research team hypothesizes and anticipates MCAT to be an effective intervention for reducing burnout and promoting wellness on the basis of previous research on the subject [19–21]. A SPIRIT checklist of the RCT is provided in the Additional file 1. Consenting participants to be recruited from one study site will be randomly allocated to one of these two groups after baseline assessments have been conducted. Figure 1 details the recruitment, assessment, intervention, and follow-up procedures.

**Fig. 1 Fig1:**
[figure not shown]
Study design flowchart

### Study site

Study participants will be recruited from the largest homecare hospice service provider and its various satellite centers across Singapore. Specifically, HCA Hospice Care (HCA) (formally known as the Hospice Care Association) is a registered charity that offers homecare and daycare hospice services to terminally ill patients and their families. With one major daycare center (which also serves as the headquarters) and four satellite service centers stationed across the country, they provide nationwide coverage to all Singapore residents who have a diagnosed life-limiting illness. Apart from offering medical care to patients of all ages, HCA provides psychological support and bereavement support services for patients and their families. HCA employs a team of about 60 palliative care specialists, including physicians, nurses, social workers, counselors, allied health professionals, personal care workers, and program staff, to provide round-the-clock support to individuals and families facing the end of life.

### Participants

The sample will comprise 60 EoL care professionals. Recruitment will be conducted at all five HCA service centers (i.e., one daycare and four satellite service centers) concurrently via four non-overlapping consecutive recruitment rounds. Each round will recruit 14 or 16 participants; seven or eight participants will be randomly assigned to one intervention group, and seven or eight participants will be randomly assigned to one control group, adhering to a waitlist RCT design. Participants will be recruited through the medical director of HCA and his appointed staff with the support of a study initiation presentation conducted by the research team during a regular monthly organization meeting with all clinical and program staff. This presentation serves as a study invitation, informing potential participants of MCAT’s basic background and essential research procedures, and includes the request for participants to keep their MCAT experiences private until study completion so as to reduce the potential for intervention contamination. Participants will be invited to join the research with the understanding that they will be given allocated time during regular working hours to participate in the MCAT intervention without any financial implications on their part; they are also assured that refusal to participate is respected and would not result in any negative consequences. Inclusion criteria include EoL care professionals (at least 21 years old) who are fluent in written and spoken English. Exclusion criteria include the inability to provide informed consent or major depression (or other mental health conditions) or both. Written informed consent will be obtained from all participants before study participation. Participants’ confidentiality will be safeguarded under this ethical provision.

### Randomization

Simple randomization for each recruitment round will be conducted by using an allocation sequence based on a computer-generated list of random numbers. Specifically, a random number sequence ranging from 1 to 14 or 16 (depending on the number of participants recruited in each recruitment round) will be generated via Research Randomizer [30]. Thereafter, each participant will be randomly assigned a unique number from the sequence. Participants whose numbers occupy the first seven or eight slots in the sequence will be assigned to the intervention group whereas participants whose numbers occupy the last seven or eight slots will be assigned to the waitlist-control group.

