### Sample size calculation

Given an attrition rate of 15% at follow-ups, a sample of 60 (*N* = 60) will provide 80% power to detect an effect size of 0.8 (referencing highly effective psychotherapy studies) [31] on the primary outcome measure of the Maslach Burnout Inventory–General Survey (MBI-GS) [4] between the intervention and control groups at a (two-tailed test) 5% level of significance.

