### Data analysis

#### Quantitative data

All quantitative data will be entered, stored, and analyzed by using SPSS statistical analysis software. Between- and within-subject comparisons of outcomes will be conducted by using repeated-measures analysis of variance (ANOVA) with the appropriate confidence interval and effect size estimates reported. Intervention and waitlist-control groups will be compared to assess intervention effectiveness on the primary outcome of burnout (continuous variable); secondary outcomes, including death attitude, emotional regulation, resilience, compassion, and quality of life (continuous variables), will also be compared to examine the potential effects of MCAT on other domains of psycho-socio-spiritual well-being. Between-subject comparisons will be conducted at T2 with baseline assessment. To explore the potential maintenance of intervention effects, within-subject comparisons will be conducted with the intervention group at T3 with baseline assessment. To examine the overall intervention effects of MCAT, within-subject comparisons will be conducted by combining the baseline-to-T2 assessment scores for the intervention group and the T2-to-T3 assessment scores for the waitlist-control group. Multi-level analysis will be conducted to characterize and predict changes in all outcomes. Intervention and waitlist-control groups will also be compared on demographic characteristics and baseline measures. If necessary, these will be controlled in the analyses. Exploratory analyses on the influence of nature or work and years of professional EoL care experience on main outcomes and secondary outcomes will also be carried out. Finally, recruitment rates as well as comparisons of dropout rates and missing data in the two groups will be reported.

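### The allocation labelled simple is a forced 1:1 split within each of four recruitment rounds, and no analysis names a round term; if change differs by round, the arm comparison is mildly conservative

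*Protocol article*

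**What the plan says.** All references are to the protocol article.

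- **Randomization** gives the label: "Simple randomization for each recruitment round will be conducted by using an allocation sequence based on a computer-generated list of random numbers". It then describes putting the numbers 1 to 14 or 1 to 16 in random order and splitting the order in half: "Participants whose numbers occupy the first seven or eight slots in the sequence will be assigned to the intervention group". The remaining half goes to the waitlist.
- **Participants** places this in "four non-overlapping consecutive recruitment rounds" and repeats the fixed numbers: "Each round will recruit 14 or 16 participants; seven or eight participants will be randomly assigned to one intervention group", with the same number going to control. The total is fixed too: "The sample will comprise 60 EoL care professionals".
- **Quantitative data** names the main method: "Between- and within-subject comparisons of outcomes will be conducted by using repeated-measures analysis of variance (ANOVA"). The arms are compared at T2 relative to baseline. Demographic characteristics and baseline measures may be controlled for where that is judged necessary. A multi-level analysis is also announced, but its levels are not given. Recruitment round appears nowhere in the section.

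**The concern.** Under simple randomisation each person is allocated independently, and the arm sizes are left to chance. Here the arm sizes are fixed in advance within each round, so round is a stratification factor. The label contradicts the mechanism beside it, and a reader who relies on the label will expect an analysis of one unstratified pool.

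When balance on a factor is forced, differences along that factor no longer contribute to the error of the arm contrast. A model without the factor still counts them in the residual variance, so intervals are wider and power lower than the design allows. The article's only stated route to covariate adjustment is a comparison of the arms on demographics and baseline measures. Round is balanced by construction, so such a check would never bring it in.

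Round differences are plausible. The rounds are consecutive, the research period is 48 months (Trial status), and the target sample is about as large as the site's team of roughly 60 (Study site). Power is a real constraint, because the Discussion lists the small sample and the large assumed effect as limitations.

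**Working it through.** **1. The plan's own sample size.** Inputs from Sample size calculation: effect size 0.8, two-sided 5%, 80% power, 15% attrition. Per arm, n = 2 × (1.960 + 0.842)² / 0.8² = 24.5, rounded up to 25. Then 25 / 0.85 = 29.4, rounded up to 30 per arm, or 60 in total. With the t distribution, 25.52 per arm are needed. The 60 × 0.85 = 51 completers (25.5 per arm) give 79.96% power. The stated figure reproduces.

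**2. Is the mechanism simple randomisation?** Four rounds of 14 or 16 that total 60 must be two of each (2 × 14 + 2 × 16 = 60). Under independent 1:1 allocation, exact balance has these probabilities:

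- round of 14: C(14,7)/2¹⁴ = 0.209
- round of 16: C(16,8)/2¹⁶ = 0.196
- all four rounds: 0.209² × 0.196² = 0.0017

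The described procedure gives exact balance every time, so it is not simple randomisation.

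**3. What does leaving round out cost?** With two time points, the group-by-time test of a repeated-measures ANOVA is a comparison of change scores. The relevant quantity is therefore the share ρ of the variance in six-week change that lies between rounds. The documents give no value, so 0 to 0.20 is assumed.

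Take 52 completers in rounds of 12, 12, 14 and 14, which is 15% attrition rounded to equal arms. Each arm has 26 people, split 6, 6, 7 and 7.

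- Expected residual variance with round in the model: 1 − ρ.
- Expected residual variance without it: (1 − ρ) + cρ, where c = (1 − Σw²) × 26/25. Here Σw² = (36 + 36 + 49 + 49)/676 = 0.2515, so c = 0.778.
- Ratio of standard errors: √[1 + cρ/(1 − ρ)]. This is 1.008 at ρ = 0.02, 1.020 at 0.05, 1.042 at 0.10 and 1.093 at 0.20.

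A simulation of this setting (20,000 runs per row) agrees:

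| Assumed ρ | SE without round | SE with round | Type I error without | Power at 0.8, without | Power at 0.8, with |
|---|---|---|---|---|---|
| 0 | 0.276 | 0.276 | 5.1% | 80.5% | 80.4% |
| 0.02 | 0.275 | 0.273 | 4.9% | 81.5% | 81.8% |
| 0.05 | 0.274 | 0.269 | 4.5% | 81.7% | 82.6% |
| 0.10 | 0.273 | 0.262 | 4.0% | 82.7% | 84.5% |
| 0.20 | 0.269 | 0.247 | 3.6% | 84.2% | 88.5% |

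With round in the model, type I error is about 5% throughout. A second, separate simulation with 52 completers gave power of 81.0% vs 80.9% at ρ = 0, 82.3% vs 84.5% at 0.10 and 84.9% vs 88.9% at 0.20.

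**4. Can the arm difference be read round by round?** Completers per arm per round: 60 × 0.85 / 8 = 6.4. The 95% half-width is at least 1.96 × √(2/6.4) = 1.10 SD, wider than the design effect of 0.8 SD.

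**The case against.** The case on the other side is substantial, and much of it stands.

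- **The analysis may contain round.** A reader might infer that the trial will be analysed with no round term. The article does not support that: the levels of its multi-level analysis are unstated, and the full protocol and SAP are not shown. What can be said is that no round term is named.
- **The mismatch is conditional.** A reader might infer that the standard errors are wrong whatever happens. They are too large only if change differs by round. Stable differences, such as keener staff joining first, largely cancel in a contrast taken relative to baseline, so the upper end of the assumed range may be generous.
- **The error is in the safe direction.** Round omission by itself does not inflate false positives, and unadjusted power in the table stays above 80%.
- **A fading contrast is not detected.** Between 44 (60 − 16) and 46 (60 − 14) people will have enrolled before round four, so one might expect a round term to show whether the arm difference shrinks as colleagues receive MCAT. A round main effect cannot show this, and step 4 shows that estimates by round are too imprecise to settle it.
- **Clustering acts the other way.** MCAT is delivered in groups of seven or eight. At an assumed round share of 10% and a treated-group intraclass correlation of 0.05, simulated type I error is about 6% without a round term and 7% with it. The round term removes an accidental offset and does not cure the clustering.

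The objection that the label does little harm, because the procedure is spelled out beside it, is fair as to reproducibility. The label still contradicts the text, and no unseen document can change that.

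**Conclusion.** The label is wrong on the face of the article: allocation is restricted, 1:1, and stratified by four recruitment rounds. The analysis section names no term for that stratification, and its stated rule for choosing covariates would not select round.

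The consequence is modest and conditional. If six-week change differs between rounds, the unadjusted standard error is too large by about 2%, 4% and 9% at assumed round shares of 5%, 10% and 20%, and about 1, 2 and 4 percentage points of power are forgone. At zero round variance there is no loss. These figures rest on assumed shares, 52 completers, equal attrition across arms and rounds, and no clustering by MCAT group. The point concerns correct description and efficiency; it does not show an invalid test or an excess of false claims of benefit.

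**What to change.** 1. In Randomization, replace the label with a description of 1:1 restricted randomisation, one block of 14 or 16 per recruitment round.
2. In Quantitative data, include round (four levels) as a fixed factor in the between-arm T2 comparison of the primary and secondary outcomes, as a consequence of the design and not subject to a baseline check.
3. State how clustering within MCAT groups will be handled. Decide this separately and alongside item 2, because the round term does not deal with it.
4. If the arm difference is shown by round, mark it as descriptive only, since each round has about 6 to 7 completers per arm.

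Items 1 and 2 cost a change of wording and 3 degrees of freedom (50 to 47 residual with 52 completers). The sample size of 60 is unchanged, and round follows from the recruitment process, so no new data are needed.
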